# Comparing the effectiveness of copper intrauterine devices available in Canada. Is FlexiT non-inferior to NovaT when inserted immediately after first-trimester abortion? Study protocol for a randomized controlled trial

**DOI:** 10.1186/1745-6215-13-147

**Published:** 2012-08-24

**Keywords:** Contraception, Intrauterine device, Intrauterine device expulsion, Contraception effectiveness, Abortion-induced, Therapeutic abortion, Non-inferiority trial, Randomized controlled trial, Canada

## Abstract

**Background:**

We describe the rationale and protocol for a randomized noninferiority controlled trial (RCT) to determine if the Flexi-T380(+) copper intrauterine contraceptive device (IUD) is comparable in terms of effectiveness and expulsion rates to the most common Canadian IUD currently in use, NovaT-200, when placed immediately after a first-trimester abortion.

**Methods/Design:**

Consenting women choosing to use an IUD after an abortion for a pregnancy of less than 12 weeks of gestation will be randomized to device-type groups to receive immediate post-abortion placement of either a Flexi-T380(+) IUD, a device for which no current evidence on expulsion or effectiveness rates is available, or the Nova-T200 IUD, the only other brand of copper IUD available in Canada at the time of study initiation. The primary outcome measure is IUD expulsion rate at 1 year. Secondary outcomes include: pregnancy rate, method continuation rate, complication rates (infection, perforation), and satisfaction with contraceptive method. A non-intervention group of consenting women choosing a range of other post-abortion contraception methods, including no contraception, will be included for comparison of secondary outcomes. Web-based contraception satisfaction questionnaires, clinical records, and government-linked health administrative databases will be used to assess primary and secondary outcomes.

**Discussion:**

The RCT design, combined with access to clinical records at all provincial abortion clinics, and to information in provincial single-payer linked administrative health databases, birth registry, and hospital records, offers a unique opportunity to determine if a novel IUD has a comparable expulsion rate to that of the current standard IUD in Canada, in addition to the first opportunity to determine pregnancy rate and method satisfaction at 1 year post-abortion for women choosing a range of post-abortion contraceptive options. We highlight considerations of design, implementation, and evaluation of the first trial to provide rigorous evidence for the effectiveness of current Canadian IUDs when inserted after first-trimester abortion.

**Trial registration:**

ClinicalTrials.gov Identifier NCT01174225

## Background

This randomized non-inferiority controlled trial (RCT) will examine the effectiveness of post-abortion contraception by determining whether a new type of copper intrauterine device (IUD) in Canada has a comparable effectiveness and safety profile to the most commonly used Canadian IUD. Clinical experience suggests that expulsion rates may vary significantly between devices, but we have been unable to find any published evidence estimating expulsion rate or pregnancy rate for this new IUD. Our results will provide some evidence of whether the new IUD is comparable with the current standard, and provide the first prospective rigorous evaluation of effectiveness at 1 year for post-abortion contraceptive methods currently available in Canada.

Nearly a third of Canadian women have at least one abortion 
[1]. Annually about 100,000 abortions are performed in Canada 
[2]. In 2009, at least 30.7% of these were repeat abortions 
[3]. Women having repeat abortions are more likely to be from ethno-cultural minorities, to report problems with a male partner, to have a lower level of education, and to have other children at home 
[4,5]. Thus, research to delineate methods to prevent recurrent unwanted pregnancies in this vulnerable population is a high priority. Ames 
[6] found a 5-year repeat abortion rate of 9.4% for Canadian women who had an IUD (Flexi-T380(+)®; Prosan International BV. Arnhem, The Netherlands) 
[7] placed immediately after a first-trimester abortion. However, this retrospective study was only able to determine the recurrent abortion rate of women returning to the index abortion clinic; thus, it is possible that the number of pregnancies was significantly higher than the number of repeat abortions reported. Even so, the reported repeat abortion rate of 9.4% is significantly higher than would be expected based on evidence for the post-abortion effectiveness of a copper IUD 
[8,9]. Overall 5-year pregnancy rate for IUD users is estimated to be less than 2% 
[10-12], or a repeat abortion rate of 35 per 1000 women-years of follow-up for women with other models of IUD placed post-abortion 
[13]. Indeed, the placement of copper IUD types available in other jurisdictions as an effective contraception method following a first-trimester (before 12 weeks of gestational age) abortion is well supported by systematic reviews 
[8,14].

The only copper IUDs available in Canada at the time this study began were the Nova-T (Nova-T200®; Bayer Inc, Canada), and two Flexi-T devices (Flexi-T300® and Flexi-T380(+)®; both Prosan International BV) 
[7]. Canadian physicians report higher rates of expulsion with the Flexi-T devices 
[6,15] and yet many prefer the Flexi-T380(+) because evidence supports copper devices with a surface area of 380 mm as being more effective than those with an area of 200 mm 
[10,14,16-19]. We found no reports in the literature describing the expulsion rates or effectiveness for the Flexi-T devices, although reported outcomes for NovaT200 are available 
[16-19].

This RCT will determine if the Flexi-T380(+) copper IUD (referred to hereafter as ‘FlexiT’) is comparable with the most common Canadian copper IUD currently in use, the NovaT-200 copper IUD (referred to as the ‘NovaT’), when placed immediately after a first-trimester abortion. Additionally, we will report the first rigorous evidence for the effectiveness of, and satisfaction with, the range of post-abortion contraceptive options available to Canadian women.

## Methods/Design

### Study design

This prospective non-inferiority randomized controlled study will recruit women at the time of an abortion at gestational age of less than 12 weeks (first trimester). Consenting women choosing to use an IUD post-abortion will be randomized to type of device, and women choosing other post-abortion contraceptive methods, or no method of contraception, will be enrolled in a non-intervention, observational arm. Primary outcome will be rate of expulsion at 1 year. Secondary outcomes will include rates for pregnancy; complications such as infection or perforation; continuation of, and satisfaction with, the chosen contraceptive method as determined at 1, 2, 3, 4 and 5 years; and expulsion rate for each type of copper IUD at 2, 3, 4 and 5 years.

### Sample-size justification for comparing expulsion rates for the NovaT and FlexiT

Our aim in this non-inferiority study is to provide evidence that the expulsion rate for the Flexi-T does not exceed that of the Nova-T by more than 10%. The rationale for this choice rests on the assumption that the detection rate for IUD expulsions is at least 85% 
[20], which implies that the loss in efficacy of a device due to expulsions is less than 0.15 times its expulsion rate, and correspondingly, that any difference in efficacy between devices is less than 0.15 times the difference in expulsion rates. Thus differences of 10% in expulsion rates translate into differences in efficacy of 1.5% or less.

We calculated power calculations for non-inferiority testing following the approach described by Blackwelder 
[21] using the on-line calculator provided by S. Patten 
[22].

Our null hypothesis is: H_0_: FlexiT expulsion rate ≥ NovaT expulsion rate + 10%.

This formula requires specification of the problem in terms of success proportions (that is, those not experiencing expulsion by 1 year). We will assume the rate of those not experiencing expulsion will be 96% for the Nova-T 
[17-19] and 92% for the Flexi-T. Thus, we require a sample size of 192 per group to attain 80% power at α = 0.05 to detect a difference in expulsion rates exceeding 10%. We will enroll a total of 400 women, a sufficient number to allow for changes to intention to leave the province and thus loss to follow-up using the health administrative databases. This recruitment will ensure the final sample is at least the 384 women required to test the null hypothesis that FlexiT has a significantly inferior (higher) expulsion rate compared with the NovaT.

Thus, our recruitment will include 400 women who choose to have IUDs and consent to be randomized to either the Flexi-T (200 women) or the Nova-T (200 women), and a further 200 who decide to not to use intrauterine contraception, who will be enrolled as a non-intervention comparator group. Therefore, a total of 600 women will be recruited.

The study clinic (see ‘Recruitment facility’, below) provides abortions to about 700 women meeting the entry criteria each year, and based on our previous research in this setting 
[23] we expect 40% of eligible women to choose an IUD, and 80% of these to enroll in IUD groups. Target enrollment is anticipated at 22 months.

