#### Expulsions

Most women will be aware when an IUD expulsion occurs 
[20], and should it occur, will make arrangements for alternative contraception. This alternative contraception may be a replacement device or a change in contraceptive method. Each participant will be provided with a toll-free number enabling them to contact the principal investigator ([name]) at any time. In addition, the study team will monitor follow-up visits, CSQs, government medical plan billings, and prescription records of alternative contraception prescribed or an IUD removed or inserted. In this manner, we believe we will be able to estimate device expulsion rate with a fair degree of accuracy. To reflect usual contraceptive conditions most accurately in the event of an expulsion, we are not providing a free replacement device. We have stratified at randomization for parity, as this may be a confounding factor in expulsion.

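### The 1.5% cap on the efficacy difference is stated as a general bound but holds only under unstated conditions, so non-inferior expulsion does not by itself show comparable effectiveness

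*Protocol article*

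**What the plan says.** The section on sample-size justification sets the null hypothesis as "FlexiT expulsion rate ≥ NovaT expulsion rate + 10" percentage points. Its reason for that margin has three steps. It assumes that "the detection rate for IUD expulsions is at least 85" per cent. It infers that "the loss in efficacy of a device due to expulsions is less than 0.15 times its expulsion rate". It then carries this over to the comparison: "any difference in efficacy between devices is less than 0.15 times the difference in expulsion rates", and so "differences of 10% in expulsion rates translate into differences in efficacy of 1.5% or less". The article gives no other reason for the margin.

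Other sections bear on the argument:
- The Background reports evidence that copper devices of 380 mm surface area are more effective than those of 200 mm. The two trial devices differ in this way.
- The Enrollment process section says that the devices' strings differ in number and consistency.
- The Expulsions section expects women who notice an expulsion to arrange other contraception, by a new device or another method, and adds that "we are not providing a free replacement device".
- The Abstract describes the aim as finding out whether FlexiT "is comparable in terms of effectiveness and expulsion rates to the most common Canadian IUD currently in use". The Background and Contribution sections also speak of comparable effectiveness, and of non-inferiority for post-abortion contraception.

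**The concern.** The third step treats an upper limit on each device's loss as if it were the loss itself. If one loss is below 0.15 times A and the other is below 0.15 times B, their difference need not be below 0.15 times (A minus B), because the second loss may be far below its own limit. The sentence also covers any efficacy difference, although the argument considers only losses through unnoticed expulsions.

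At stake is how the result will be read. The 1.5% is the only stated link between a margin on expulsion and the wider aim of comparable effectiveness. If it is quoted as a guarantee, a non-inferior expulsion result will seem to limit the efficacy difference more tightly than the premise allows.

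**Working it through.** **Inputs, all from the sample-size section.** Margin 10 percentage points; detection at least 85%, so an undetected share u between 0 and 0.15 for each device; NovaT expulsion E_N = 4% (96% without expulsion); FlexiT planning rate E_F = 8% (92% without expulsion). At the margin, E_F = 4% + 10% = 14%.

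**Reproducing the 1.5%.** If both devices share one undetected share u ≤ 0.15, and only undetected expulsions cost efficacy, the difference in loss is u × (E_F − E_N) ≤ 0.15 × 10% = 1.5%. The figure reproduces under those conditions.

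**Without equal detection.** The difference in loss is u_F × E_F − u_N × E_N, with each u anywhere from 0 to 0.15. It is largest at u_F = 0.15 and u_N = 0, so the valid bound is 0.15 × E_F.

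| NovaT / FlexiT expulsion | Protocol rule 0.15 × (E_F − E_N) | Bound from the premise 0.15 × E_F |
|---|---|---|
| 4% / 14% (margin) | 1.5% | 2.1% |
| 4% / 8% (planning rates) | 0.6% | 1.2% |
| 4% / 4% | 0 | 0.6% |

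At the margin, with FlexiT detection at 85%:
- NovaT detection 100%: 2.1% − 0 = 2.1%
- NovaT detection 95%: 2.1% − 0.05 × 4% = 1.9%
- NovaT detection 90%: 2.1% − 0.10 × 4% = 1.7%
- NovaT detection 85%: 2.1% − 0.15 × 4% = 1.5%

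All four cases satisfy the protocol's premise. Only the last one respects its cap.

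**Loss after noticed expulsions.** Let q be the efficacy loss per undetected expulsion and r the loss per detected one. The documents give neither, so both are assumptions. With common 85% detection the difference at the margin is 10% × (0.15q + 0.85r). Taking q = 1:
- r = 0: 1.5%
- r = 2%: 10% × (0.15 + 0.017) = 1.67%
- r = 5%: 10% × (0.15 + 0.0425) = 1.93%
- r = 10%: 10% × (0.15 + 0.085) = 2.35%

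The factor 0.15 also has slack when q is below 1. With r = 0, the worst case above is 2.1% × q, which stays under 1.5% when q < 1.5/2.1 = 0.714.

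**In-situ efficacy.** A difference due to copper area is not in the formula at all. On the evidence cited in the Background it would favour FlexiT. It therefore contradicts a cap on any difference without pointing to harm from FlexiT.

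**Sample size.** (0.96 × 0.04 + 0.92 × 0.08) × (1.645 + 0.842)² / (0.10 − 0.04)² = 0.112 × 6.183 / 0.0036 ≈ 192.3 per group, against 192 stated. The calculation uses the margin but not the 1.5%, so it is unaffected.

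**The case against.** The strongest reply is that the section speaks of the detection rate in the singular. Read as one rate for both devices, it makes 1.5% correct. The 2.1% is an extreme corner: every NovaT expulsion noticed, FlexiT detection at exactly 85%, and full efficacy loss in every unnoticed case. The null hypothesis and the decision rule in Analysis methods concern expulsion only, and pregnancy is measured directly as a secondary outcome. No section says that effectiveness will be inferred from the expulsion test.

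Much of this stands, and it limits the point. It does not rescue the sentence, because a lower limit on detection is not a statement that detection is equal, and the cap is worded to cover any difference.

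A reader might be tempted by stronger readings that the documents do not support:
- *That the arithmetic is wrong or the margin is invalid.* The product is correct. What fails is the inference from the premise, and nothing shows that 10% is untenable for expulsion itself.
- *That the strings prove unequal detection.* The Enrollment process section mentions them to explain why blinding is impossible. It says nothing about how often women notice an expulsion.
- *That lack of a free replacement means noticed expulsions go uncovered.* The Expulsions section expects women to make other arrangements and presents the choice as reflecting usual conditions. No rate of uncovered expulsions is given.
- *That 1.5% in one year is alarming beside the quoted 5-year pregnancy rate of under 2%.* The same sentence of the Background also gives 35 repeat abortions per 1000 women-years after post-abortion placement of other IUD models, or 3.5 per 100. That benchmark gives a very different impression.

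**Conclusion.** The point holds as an overstated bound. The 1.5% is valid if detection is equal, noticed expulsions cost nothing and in-situ efficacy is the same. The sample-size section states none of these conditions, and the last conflicts with the Background. On the stated premise alone, the expulsion-related difference at the margin is bounded by 2.1% for a NovaT rate of 4%, a worst case that moves with the NovaT rate. Loss after noticed expulsions would come on top, by an amount the documents do not allow one to fix. Incomplete loss after unnoticed ones would work the other way.

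The consequence is for interpretation. The expulsion test is internally consistent and can support a conclusion on expulsion. The 1.5% cannot carry that conclusion over to comparable effectiveness.

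**What to change.** In the margin rationale, limit the sentence to expulsion-related loss. Give 1.5% as conditional on equal detection for both devices and no loss after noticed expulsions. Add 2.1% as the worst-case bound without equal detection, at NovaT 4% and FlexiT 14%, still with no loss after noticed expulsions.

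In the statements of aim and contribution, confine non-inferiority to expulsion. Base any statement on comparable effectiveness on the 1-year pregnancy rates already planned as a secondary outcome, reported as a difference with its confidence interval and described as not powered for non-inferiority.

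The cost is wording and a slightly less favourable figure in the rationale. Margin, sample size, data collection and conduct stay as they are.

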### Inclusion criteria

All women at participating study sites who have completed informed consent for an abortion at less than 12 weeks gestational age (as determined by ultrasonography) and who are residents of the Canadian province of British Columbia (BC) enrolled in the universal provincial medical services plan are eligible to participate. Additionally, those who have chosen to use an IUD for post-abortion contraception are eligible to be randomized to the device groups. The study has no minimum age criteria for enrollment.

### Exclusion criteria

Women are not eligible if they intend to move from BC within the next year, if they intend to conceive within 1 year, or if they are currently enrolled in another clinical trial. The contraindications to the use of an IUD are also exclusion criteria.

•Uterine cavity anomalies causing distortion of the endometrial canal including fibroids of more than 50 mm, excluding repaired uterine septum.

• Wilson’s disease.

• Current untreated pelvic inflammatory disease, cervicitis, or lower genital tract infection.

• Undiagnosed abnormal uterine bleeding.

• Known uterine or cervical malignancy or cervical dysplasia.

• Bacterial endocarditis.

• Established immunodeficiency (HIV positivity is not an exclusion unless immunodeficiency is present).

• Acute malignancies affecting blood or leukemias.

• Recent trophoblastic disease with raised levels of human chorionic gonatotropin.

Post-randomization exclusion factors for women in the randomized groups include perforation or excessive bleeding at the time of their abortion, failure to undergo the abortion procedure for any reason, or a uterine anomaly detected at the time of the abortion procedure. These exclusions are designed to be only those that, in real-life clinical practice, would preclude a woman from being able to use an IUD as an immediate method of contraception.

### Recruitment facility

Recruitment for this study will be undertaken at a teaching-hospital outpatient abortion service in the Canadian province of British Columbia (BC).

### Enrollment process

All women presenting at the study clinic for an abortion of a pregnancy before 12 weeks gestational age will receive information via the research study web page 
[24] at the time they book their appointment, and a study information brochure upon check-in. All women will undergo a post-abortion contraception information session with a trained clinic nurse who is not part of the research staff, and the women will decide upon their contraceptive method of choice before they are asked if they wish to participate in the study. Interested potential participants will then be referred for an information session with a trained women’s health research assistant (RA). The RA will explain all study procedures, answer all questions, and complete the informed consent process with women before the time of their abortion, including establishing preferred personal contact methods to ensure follow-up. Enrolled women will complete an intake version of the contraception satisfaction questionnaire (CSQ) on site. We have previously described the development and use of the CSQ 
[23]. Briefly, this is a detailed instrument eliciting the effectiveness of, degree of satisfaction with, and adverse effects experienced for the range of contraceptive methods available in Canada. The CSQ has been adapted from a published instrument 
[25,26] for use in post-abortion studies. It has been translated into the three most common non-English languages in our study population, and piloted for accuracy and cultural sensitivity. This trial has been registered at ClinicalTrials.Gov (Identifier: NCT01174225).

Participants choosing a copper IUD will be randomized to receive either the Flexi-T or the Nova-T. Stratified (that is, separate) randomization lists in sequential blocks of sizes of eight will be generated for parous and nulliparous women. Allocation will be performed remotely using a Canadian on-line randomization service (http://www.randomize.net 
[27]), to maintain strict concealment. Staff will be kept unaware of the randomization design and of stratification factors involved, to mitigate the potential for unblinding of individual blocks. For women choosing an IUD, the study device determined by the randomization will be inserted by their surgeon immediately after the abortion and before the worman leaves the procedure or operating room. Blinding of the surgeon or the woman receiving the IUD is not possible, as the IUDs are distinct in appearance. Even once *in situ*, these two devices have a differing number and consistency of strings palpable at the cervical os. Following standard clinic protocol, all women will undergo PCR testing for chlamydia and gonorrhea before their abortion, and receive 2 g metronidazole as a single observed dose as prophylaxis against postoperative infection 
[28]. Women deemed to be at higher risk of a sexually transmitted infection (STI) 
[28] and those with positive PCR results will receive 1 g of azithromycin as well. A post-placement ultrasound image of the IUD *in situ* will be recorded.

Participants choosing no contraception and all other methods of contraception will receive normal instructions from the facility physician for implementation of their contraceptive method, undergo the same STI testing and prophylaxis protocol, and complete an intake CSQ before leaving the abortion facility.

Enrolled participants will complete the subsequent CSQ either by mail or as a web-based questionnaire at 3, 6, and 12 months post-abortion. User-friendly internet-based and paper-based formats are available for each of the four most common languages spoken in our study population.

All recruited women will receive reimbursement for their time in the form of a gift certificate at enrollment and for each completed CSQ submitted. In addition, women choosing to be randomized to an IUD arm will receive their device free of charge.

